## Methods/design

Preterm SAMBA, an international collaborative multicentre study for the development of predictive tests that translate into clinical care, can be divided into two distinct phases: The first component (Discovery phase) is a case–control study that aims to identify clinical and metabolomics biomarkers related to spontaneous preterm birth. For this initial phase, untargeted metabolomics techniques will be employed to identify and quantify potential predictor’s metabolites that can be associated to potential clinical predictors. The second component (Validation phase) is a cohort study developed to validate the algorithm of prediction using the clinical and metabolomics biomarkers discovered in the first component of the study. Thus, to evaluate the performance of the prediction model developed at the first phase, targeted metabolomics techniques will be employed to analyse participants’ blood and hair samples to quantify those specific metabolites identified as potential predictors of preterm birth.

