### Validation phase – the Brazilian multicentre cohort study

The Preterm SAMBA validation phase consists of a Brazilian multicentre cohort study with 1150 low-risk pregnant nulliparous women. Five of the 27 members of the Brazilian Network for Studies on Reproductive and Perinatal Health (BNSRPH), were chosen to participate in the Brazilian cohort (Table 3). Previous excellence performance in epidemiological and translational studies and diversity of cultural, ethnical and sociodemographic population characteristics were criteria for centre selection. Therefore, there are participating centres in three of the five regions of Brazil, which are the three most populated regions of the country: Northeast, Southeast and South.

**Table 3 Tab3:** Participating centres in the Preterm-SAMBA study validation phase – Brazilian cohort

Maternity of CAISM, University of Campinas, in Campinas, São Paulo.	
Maternity of the School of Medicine from UNESP, in Botucatu, São Paulo.	
Maternity of the Clinic Hospital, Federal University of Rio Grande do Sul, in Porto Alegre, Rio Grande do Sul.	
Maternity of the Clinic Hospital, Federal University of Pernambuco, in Recife, Pernambuco.	
MEAC – School Maternity of the Federal University of Ceará, in Fortaleza, Ceará.	

Assuming a type I error rate, α, of 5 % and an estimated area under ROC curve of at least 0.68, then in order to test hypotheses to a suitable level of power (80 % power, β = 0.2), the sample size sufficient should approximate to 80 cases of spontaneous preterm birth (<34 weeks gestation), calculated using MEDCALC®. Based on a minimum expected preterm birth rate of 7 %, the total cohort size should therefore be of approximately 1150 subjects, around 230 women at each participating centres.

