*Postpartum data:* data will be collected from the participant’s medical record, the prenatal chart and/or from a personal interview with the participant during hospital admission to minimize missing information. The main outcome is spontaneous preterm birth, defined as a birth before 34 weeks of gestational age due to preterm labour or premature rupture of membranes. Secondary outcomes will also be evaluated: spontaneous preterm birth alternatively defined as a birth before 37 weeks of gestational age due to preterm labour or premature rupture of membranes, provider-initiated preterm birth, defined as preterm birth due to medical indication on account of maternal or fetal conditions; pre-eclampsia, defined as having systolic blood pressure ≥ 140 or systolic blood pressure ≥ 90 mmHg after 20 weeks gestation on at least two occasions apart of 20 min, and/or proteinuria (24-h urinary protein ≥ 300 mg or urine dipstick ≥ ++) and/or severe maternal complications [32]; gestational diabetes mellitus according to ADA guidelines [33]; fetal growth restriction (FGR) defined as having birthweight below 10th percentile based on GROW customised birthweight centiles [34]. Clinical data will also be collected regarding the occurrence of preterm labour, cervical cerclage, deep vein thrombosis, infection, vaginal bleeding, dipstick proteinuria, intercourse, hospital admission, deep vein thrombosis during pregnancy and puerperium, and maternal mortality and the use of progesterone and/or pessary, tocolytic, antibiotic for preterm labour or pPROM, corticosteroids for fetal maturation, magnesium sulphate for neuroprotection during pregnancy. The occurrence of severe maternal morbidity and near miss will also be reported according to WHO guidelines [35]. Neonatal outcomes related to neonatal morbidity and mortality will be recorded until newborn discharge or death.

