#### Metabolomics analysis

The precise methodology to be used in the validation phase will depend on the ongoing discovery studies. As detailed above we anticipate that it will be based on a targeted triple quad MS (QQQ-MS) platform, as previously described [38]. We will subsequently describe details relating to metabolomics analysis techniques and metabolomics statistical analyses. We anticipate that data analysis will be integrated into the relational database such that decision rules may combine both clinical and spectrometric data.

The performance of the final algorithm developed in the discovery phase will be evaluated by its capacity to predict spontaneous preterm birth occurrence in women from the Brazilian cohort. The validation will be performed using the average squared difference between predicted and observed outcome (R^2^), adjusted R^2^ (same as R^2^, but penalizes for the number of predictors), sensitivity, specificity, positive and negative predictive values, likelihood ratio and the area under the ROC curve.

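### The protocol defines R² as the mean squared prediction error, which runs the opposite way to R², and adds an adjusted R² whose penalty has no basis if the discovery algorithm is applied unchanged

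*Protocol article*

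**What the plan says.** The last paragraph of the protocol article's section Metabolomics analysis lists the validation measures. The first is R², explained as the "average squared difference between predicted and observed outcome". The second is adjusted R², presented as the same quantity, "but penalizes for the number of predictors". Sensitivity, specificity, predictive values, likelihood ratio and the area under the ROC curve follow.

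The outcome is binary. Under Sociodemographic, physical data and pregnancy outcomes: "The main outcome is spontaneous preterm birth, defined as a birth before 34 weeks of gestational age" (through preterm labour or ruptured membranes).

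The object under test comes from the first phase. Metabolomics analysis: "The performance of the final algorithm developed in the discovery phase will be evaluated by its capacity to predict spontaneous preterm birth occurrence". Methods/design gives the same purpose: "to evaluate the performance of the prediction model developed at the first phase". No section describes refitting the model on the Brazilian data, gives another definition of R² or mentions the Brier score.

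**The concern.** A mean squared difference between prediction and outcome measures error: a perfect algorithm scores 0 and worse algorithms score higher. R² measures the share of outcome variation explained: higher is better, and a model that gives every woman the average risk scores 0. The protocol treats the two as one. Adjusted R², being defined from the same quantity, inherits the mistake.

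Adjusted R² raises a second question. Its penalty offsets the optimism that arises when coefficients are estimated in the same data in which fit is measured. A validation that takes over a finished algorithm estimates no coefficients, so there is no such optimism to remove.

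What is at stake is how two reported performance figures are read. A reader who sees 0.06 labelled R² would take it as modest explained variation, although a model with no information scores about that at a 7% event rate.

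**Working it through.** **Inputs from the protocol**
- Event rate 7%, from the sample-size paragraph of the Validation phase section: "Based on a minimum expected preterm birth rate of 7" per cent.
- About 80 cases, about 1150 women and an AUC of 0.68, from the same paragraph.
- An AUC of 0.90, used in the Discovery phase sample-size calculation and taken here only as a contrast.

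The cohort size reproduces: 80/0.07 = 1143, close to 1150, and 1150 × 0.07 = 80.5 cases. Nothing below disputes it.

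**Assumptions not in the protocol**
- Outputs are probabilities calibrated to the 7% rate, unless stated otherwise.
- The score is normally distributed with equal variance in cases and non-cases.
- The numbers of predictors k are illustrative.

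**Formulas**
- Quantity as written: B = mean of (predicted − observed)². With probabilities this is the Brier score. If the output is only yes or no, it is the misclassification rate.
- Value of B when every woman is given risk p: p(1−p).
- Scaled Brier score, an R²-type measure: S = 1 − B/[p(1−p)].
- Adjusted value: 1 − (1 − S)(n − 1)/(n − k − 1).

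**Step 1: direction of the measure.** The no-information value is 0.07 × 0.93 = 0.0651.

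| Model | B (called R² in the protocol) | S |
|---|---|---|
| No information | 0.0651 | 0 |
| AUC 0.68 | 0.0630 | 1 − 0.0630/0.0651 = +0.03 |
| AUC 0.90 | 0.0453 | 1 − 0.0453/0.0651 = +0.30 |

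B falls as the model improves while S rises. B also moves little between no information and an AUC of 0.68, because its scale is set mainly by the event rate.

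**Step 2: sensitivity to calibration.** The discovery phase is a case–control study. The abstract gives 100 cases and 100 term births; the Discovery phase section can be read as two controls per case. If the predicted risks kept that case fraction and were not corrected to 7%, then at an AUC of 0.68:

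| Case fraction carried over | B | S |
|---|---|---|
| 1/3 | about 0.13 | about −1.0 |
| 1/2 | about 0.23 | about −2.5 |

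A value of 0.23 labelled R² would look better than the calibrated model's 0.063, although the risks are far worse. The AUC is the same in both cases, because a shift of intercept does not change the ranking. The protocol does not say how the intercept is handled, so this shows what is possible, not what is planned.

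**Step 3: the adjusted version.** Take n = 1150 and S = 0.03 with the coefficients fixed beforehand:
- k = 5: 1 − 0.97 × 1149/1144 = 0.026
- k = 10: 1 − 0.97 × 1149/1139 = 0.021
- k = 20: 1 − 0.97 × 1149/1129 = 0.013
- k = 50: 1 − 0.97 × 1149/1099 = −0.014

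The predictions and their errors are identical in all four rows. Only the count of predictors changes the result.

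**The case against.** The strongest reply is that nothing decisive hangs on these two measures. The sample size rests on the AUC, the abstract's list of performance measures contains neither R² nor adjusted R², and no threshold or decision rule uses them. That stands, and it sets the severity.

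A second reply is that the authors probably meant conventional R² and described it carelessly, and that the section leaves the precise validation methodology to depend on the discovery work. The text does not settle what was meant, so a misreading is possible rather than certain. But deferring details does not correct a definition that the section itself states.

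A third concerns adjusted R². A reader might infer that it is meaningless here, or that the protocol rules out estimating any coefficient in Brazil. Neither is supported. An adjusted value can be computed. That the algorithm stays fixed is inferred from its description as the final product of the discovery phase. Markers move from untargeted methods to a targeted platform, so some rescaling or refitting is not formally excluded, although none is described and a refit would no longer validate the discovery algorithm. What stands is conditional: if the algorithm is applied unchanged, the penalty has nothing to correct.

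A fourth is that the name Brier score presumes probability outputs, while the section also speaks of decision rules. With yes/no outputs the quantity is the misclassification rate, which is still an error measure running against R².

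**Conclusion.** The definition of R² is wrong as stated, and no other part of the article corrects it. The adjusted R² inherits the error and, separately, has no basis where the discovery algorithm is carried over without re-estimation.

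The size is minor. Under a 7% event rate, calibrated probabilities and a binormal score, the mislabelled quantity moves from 0.065 to 0.045 between no information and an AUC of 0.90, while the properly scaled measure moves from 0 to +0.30. The direction of the error does not depend on those assumptions; the figures do. The scaled value of +0.03 at an AUC of 0.68 in particular holds only for calibrated risks.

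A reader might go further and conclude that the validation as a whole is compromised. The documents do not support that: the AUC, sensitivity, specificity, predictive values, likelihood ratio and the AUC-based sample size do not use R².

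**What to change.** In the last paragraph of Metabolomics analysis:

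1. Rename the measure the Brier score and state that lower is better. If the algorithm gives only yes/no classes, call it the misclassification rate.
2. If an R²-type figure is wanted, report the scaled Brier score, 1 − Brier/[p(1−p)], with p the event rate observed in the Brazilian cohort. Note that it can be negative, even for a model that discriminates, if risks from the case–control phase are not corrected to the cohort's event rate.
3. Remove adjusted R² where the discovery algorithm is applied unchanged. If any coefficients are to be re-estimated in the Brazilian data, say so and report that analysis separately from the validation.
4. Keep the remaining measures as they are.

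The cost is about one sentence of text. No data collection, sample size or other analysis changes.

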### Ancillary studies

The Preterm SAMBA Brazilian cohort study will collect additional data regarding other relevant maternal and fetal obstetric complications. Detailed clinical data related to the occurrence and severity of pre-eclampsia, fetal growth restriction and gestational diabetes mellitus will be recorded. Fetal growth restriction will be diagnosed if birthweight is below 10th customised percentile. The occurrence of severe maternal morbidity, maternal near miss and maternal mortality during pregnancy or up to discharge after delivery will also be recorded, according to WHO definitions [35].

### Ethical aspects

The SCOPE study, whose data and samples will be analysed for the Preterm SAMBA discovery phase, was approved by local ethics committees in New Zealand and Ireland and registered in the Australian and New Zealand Clinical Trial Registry (ACTRN12607000551493) [28]. All women who participated in the SCOPE study provided written informed consent and agreed to have their data and samples used in other studies. The Preterm SAMBA study has been reviewed and approved by the National Committee for Ethics in Research of Brazil (CONEP) and by the Institutional Review Board (IRB) of the coordinating centre (Letter of approval 1.048.565 issued on 28^th^ April 2015) and of all other Brazilian participating centres. All women who will be enrolled in the Preterm SAMBA Brazilian cohort (Validation phase) will sign an informed consent form, also allowing for future additional studies with their biological samples without any additional consent.

The ethical principles stated in the Brazilian National Heath Council (Resolution CNS 466/12) will be respected in every stage of this study. The anonymity of the source of information will be guaranteed and the care for the women will be provided independent of her agreement to participate in the study. All ethical principles related to biobank storage and transport will be followed according to national and international rules related to research with human beings. The study also complies with the Declaration of Helsinki amended in Hong Kong in 1989. The methodological and ethical aspects of Preterm SAMBA study protocol were developed following STROBE guidelines [39].

## Discussion

The *“Omics*” Science comprises genomics, transcriptomics, proteomics and metabolomics technologies, which each provide valuable translational surveys in biological processes. A metabolomics approach enables the evaluation of metabolic pathways and the correlation of biochemical changes related to pathophysiology of disease, providing a downstream result of gene expression and higher sensitivity to phenotype of disease [40–45]. Underlying conditions and factors related to the occurrence, severity or prognosis of diseases with complex determinants may be assessed, bringing to light the final product of organism metabolism: the metabolome [42].

The development of a two-phase metabolomics research program that includes two large cohorts of nulliparous women is not an easy task. The network collaboration is essential to develop, implement and analyse such complex data and, more importantly, to achieve reliable results. Precise protocols for sample collection, processing, storage and biobank management will be essential to assure high quality data and results.

Metabolomics profiling requires different techniques to address the detection and quantification of different classes of metabolites once there is no current method capable to identify all of them. Preterm SAMBA study will employ different untargeted techniques that require very carefully and standardized protocols for sample preparation [24]. Studying the metabolome in blood samples requires invasive collection and immediate processing. As an alternative, hair samples are non-invasive, do not need processing methods and can be stored at room temperature. Hair can, theoretically, reflect endogenous compounds and environmental exposures from many days/weeks ago. The determination of the hair metabolome is a possible approach to identify biomarkers for spontaneous preterm birth. It has already been explored in gestational diabetes and fetal growth restriction, revealing potential endogenous mechanisms involved in those pathologic conditions [36, 45].

The identification of spontaneous preterm birth predictors using multi-ethnic data/samples and the evaluation of performance in a culturally and ethnically different population is desirable and meaningful for external validation. The use of quality control records and SPREC protocol is another important recommendation for metabolomics studies due to the necessity to evaluate confounders for analytical measures such as the time between sample collection, storage and processing conditions and the occurrence of haemolysis, lipaemia and metabolic degradation on account of inadequate temperature or solar exposure [37].

In the context of translational research, metabolomics may enhance understanding of the underlying pathways, which lead to obstetric complications. Preterm SAMBA aims to identify and validate a predictive model for spontaneous preterm birth, but will also develop a biobank and database that will enable research on pre-eclampsia (PE), fetal growth restriction (FGR) and gestational diabetes mellitus (GDM). The possibility to combine biochemical, genetics and clinical information that can be large-scale and replicable empowers the development of knowledge for clinical practice in preterm birth prevention. This would be especially worthwhile and helpful for countries with a high proportion and high absolute number of preterm births as is the case of Brazil where around 12 % of all births occur prematurely [46].

A recent clustered designed study showed that 30 % of all spontaneous preterm births do not have any maternal, fetal or placental conditions identified that could be related to its occurrence [47]. The application of metabolomics techniques could be a promising approach for spontaneous preterm birth prediction, all the more in those cases of silent phenotype in which there are no known predictors. Metabolomics have been already described in other obstetric conditions as pre-eclampsia, gestational diabetes mellitus and fetal growth restriction [31, 40, 41, 45, 48, 49], showing excellent performance in terms of a discriminatory algorithm. Therefore, we believe metabolomics is a powerful and strategic key not only for preterm birth prediction, but hopefully also for its prevention. The detection of metabolic pathways related to PTB syndrome may enable the development of more accurate therapies for primary or secondary prevention of pregnant women identified as at high-risk.

At the end of the study, if we are successful in the identification of such an effective algorithm, certainly several other topics should be carefully considered. Can this knowledge be really translated into a commercially available kit for screening purposes? Would the costs derived from this process be acceptable for low and middle-income countries? How will this be made available for populations in public sector? For discussing a future implementation of such a screening strategy, the following necessary points to be covered are to know if a concrete package of interventions to reduce preterm birth among those women identified as high-risk is available, and if it is cost-effective to be supported by the public health system. Finally, in this study we are planning to transfer the technology developed for the algorithm from New Zealand to Brazil, including lab technologies for assessing the biomarkers identified by metabolomics for preterm birth. Hopefully, if this is proved to be feasible, we believe that an important step for reducing the burden of preterm birth will have been achieved.

## Abbreviations

ADA, American Diabetes Association; BMI, body mass index; CONEP, Brazilian National Committee for Ethics in Research; FAME, fatty acid methyl esterification; FDA, Food and Drug Administration; FGR, fetal growth restriction; GC, gas chromatography; GDM, gestational diabetes mellitus; LC, liquid chromatography; MS, mass spectrometry; PE, pre-eclampsia; PI, principal investigator; pPROM, preterm premature rupture of membranes; PTB, preterm birth; SAMBA, Screening and Metabolomics in Brazil and Auckland; SCOPE, Screening for Pregnancy Endpoints study; SOP, standard operation procedures; sPTB, spontaneous preterm birth; WHO, World Health Organization
